### Data Analysis

#### Overview

Prior to the testing of hypotheses and modeling of outcome data, a detailed descriptive analysis of all data collected will be performed, involving the summarization of data and the use of exploratory data analytic techniques. This preliminary exploration of the data will be used to (1) verify randomization by assessing the comparability of groups on key descriptors at baseline, (2) describe univariate and bivariate sample distributions of the data, (3) ascertain the interrelationships between variables, and (4) check for the violation of assumptions necessary for parametric statistical techniques. Specifically, appropriate statistics describing the location (eg, means and percentiles) and dispersion (eg, SDs and ranges) of the distributions of each continuous type variable will be computed for the total sample and over time (when applicable). Frequency counts and percentages will be calculated for categorical variables. Normality will be assessed graphically (eg, histograms and normal probability plots) and inferentially (eg, skewness and kurtosis divided by their SE and Shapiro and Wilk *W* statistic). Levene test for equality of variances will be used to test the assumptions for all analyses using parametric statistics to compare means. If the necessary statistical assumptions are severely violated whereby compromising the validity of the proposed statistical procedure, data transformations or alternate statistically robust approaches, such as analogous nonparametric approaches, will be used.

#### Aim 1

Aim 1 examines changes in CINV severity, self-management behaviors, functioning, QOL, cognitive representation, and health care use within the IG from baseline (T_1_) to completion of the study (T_6_). We hypothesize that the IG will report lower levels of CINV severity and health care use and higher levels of self-management, functioning, cognitive change, and QOL from baseline to the completion of the study.

Changes in primary and secondary outcomes from T1 to T6 will be assessed using linear (CINV severity, self-management behaviors, cognitive representation, and functioning), binary (resource use), and ordinal (QOL) regressions, as appropriate, within a GEE framework. All models will control for the effects of 7 demographic (age, gender, race or ethnicity, comorbidity, education level, income level, and insurance status) and 5 experiential (cancer type, emetic potential, treatment frequency, intake of IV fluids between treatment cycles, and number of home antiemetics) variables. GEE models are well suited for this type of repeated measures design, as they account for within-subject correlations between repeated measurements over time in a longitudinal design. Furthermore, GEE models are not restricted by any distributional assumptions including the assumptions of normality required by most other approaches to longitudinal analysis such as repeated measures ANOVA. Finally, GEE models provide robust parameter and SE estimates even if the working correlation structure for the data is misspaced [61]. The analysis will be 2-tailed and conducted with SAS (version 9.4; SAS Institute Inc).

#### Aim 2

Aim 2 determines the efficacy of the MAH intervention by comparing differences in primary outcomes (CINV severity and health care use) and secondary outcomes (self-management behaviors, functioning, and QOL) between the IG and control group at each follow-up visit (T_2_-T_6_) and completion of the study (T_6_). We hypothesize that the IG will report lower levels of CINV severity and health care use at T_2_-T_6_ than the control group. We hypothesize that the IG will report higher levels of self-management behaviors, functioning, and QOL at T_2_-T_6_ than the control group.

The effect of the intervention on primary and secondary outcomes at each follow-up visit and at the completion of the study will be assessed using generalized linear mixed models (GLMMs). GLMMs are an extension of general linear models allowing the study of within- and between-subjects repeated measures variations over time. GLMMs can also be used to fit normal and nonnormal response variables, as it is the case in this study. The interaction of time and treatment will be assessed by using an interaction term in the longitudinal models. All models will control for the effects of demographic and experiential variables listed in aim 1. The analysis will be 2-tailed and conducted with SAS (version 9.4).

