### Recruitment, Randomization, and Procedures

Successful recruitment and retention strategies previously established by our team will guide this study [27,34,52-54]. A stratified sampling strategy followed by randomization will be used. This sample will mirror Florida demographics and aim to recruit participants in the following percentages: female (51%), male (49%), Black (16%), Hispanic (26.4%), White (77%), and other races (7%). At both clinical sites, a research assistant will screen all new patients for eligibility using their respective electronic medical record systems. Eligible patients will be approached by the research assistant at their first chemotherapy appointment and asked to participate. In our pilot study, this timing acted as a distraction for patients while they waited for chemotherapy to start and did not interfere with treatment, nursing care, or education. In addition, prior to treatment, all patients have received standard written education regarding treatment effects and will expect CINV as a possible effect of treatment; therefore, being approached about the study is not expected to elicit anxiety. Informed consent will be obtained in a private area of the clinic open to the research assistant, and a copy of the consent form will be given to the participant.

Once informed consent is obtained, baseline measures will be completed, and participants will be randomized (IG and ACG) to either group by choosing an envelope with a group assignment. If they are randomized to the IG, the intervention will begin immediately. Regardless, participants in each group will receive standard care (1) on admission to the cancer center (receipt of standard written educational materials that patients are instructed to bring to each appointment), (2) at a treatment planning visit in the clinic (receipt of specific handouts regarding treatment and potential side effects, and (3) at time of treatment (verbal review of chemotherapy and symptom handouts by treatment center or chemotherapy nurses). Retention of all participants will be enhanced with (1) weekly follow-up telephone calls and (2) ACG offered MAH at the end of the study.

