#### Part 1: The MAH Serious Game

The game will be administered and supervised by the research assistant. Participants will play the game on an iPad at the outpatient treatment center prior to their first chemotherapy treatment. Headphones can be used to ensure privacy and limit distraction. During the game, players make decisions for the avatar based on common CINV management practices (eg, taking medication, dietary strategies, and staying hydrated; Textbox 1), which cause the avatar to become nauseated or be nausea-free.

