#### Additional Measures

##### Sociodemographic Characteristics

Sociodemographic characteristics include age, gender, race or ethnicity, comorbidity information, education level, and income level. These characteristics will be measured at T_1_ (baseline).

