##### Experiential Characteristics

Experiential characteristics include cancer diagnosis and stage, chemotherapy regimen with antiemetics, additional treatments (eg, radiation therapy), discharge antiemetic prescriptions, fluids during treatment, changes to the treatment plan (ie, delays in treatment, chemotherapy dose reductions, and changes in chemotherapy), and number of times game is played. All cancer information will be collected from the patient’s electronic medical record by the research assistant.

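### The Aim 2 efficacy models adjust for IV fluids received between cycles, a post-randomisation variable, so the arm coefficient would not estimate the total effect of assignment; home antiemetics share the problem unless fixed before randomisation

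*Protocol article*

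**What the plan says.** Data Analysis, Aim 1 lists seven demographic covariates and "5 experiential (cancer type, emetic potential, treatment frequency, intake of IV fluids between treatment cycles, and number of home antiemetics) variables". The sentence covers all Aim 1 models. Data Analysis, Aim 2, which contains the randomised comparison, then states: "All models will control for the effects of demographic and experiential variables listed in aim 1". No Aim 2 model without these covariates is described.

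On timing, Recruitment, Randomization, and Procedures says that eligible patients are approached at their first chemotherapy appointment, and then: "Once informed consent is obtained, baseline measures will be completed, and participants will be randomized (IG and ACG) to either group". For the intervention arm, Part 1: The MAH Serious Game adds: "Participants will play the game on an iPad at the outpatient treatment center prior to their first chemotherapy treatment".

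On content, the same section says that players decide for an avatar on the basis of "common CINV management practices (eg, taking medication, dietary strategies, and staying hydrated; Textbox 1".

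On measurement, Experiential Characteristics lists items taken from the medical record, among them "discharge antiemetic prescriptions, fluids during treatment, changes to the treatment plan", and gives no measurement time. Sociodemographic Characteristics, by contrast, places its variables at T1.

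**The concern.** In a randomised comparison, adjustment is safe for variables that assignment cannot have changed. A covariate that arises later may itself be altered by the arm. The arm coefficient then compares participants who ended up with the same covariate value, which is a different question from what assignment to the game achieves. Two distortions follow. Any part of the effect that shows in the covariate is removed. And if an unmeasured factor, such as susceptibility to nausea, drives both covariate and outcome, conditioning on the covariate makes the arms differ in that factor.

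Aim 2 sets out to determine efficacy, and its mixed models are the only between-arm analysis that the article specifies. The pilot, as reported in Preliminary Findings, showed small effects and no significant difference in nausea, vomiting, quality of life or health care use. Any shift in the estimate would therefore matter to how this trial is read.

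**Working it through.** The protocol states no figure for this point, so the main check is one of timing and causal role. A numerical illustration on assumed inputs follows.

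**Timing**

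1. Baseline measures are completed, assignment follows, and the intervention arm plays the game before its first chemotherapy.
2. Study Participants excludes previous cancer treatment, so no chemotherapy cycle precedes randomisation.
3. An interval between cycles therefore exists only after assignment, and between-cycle IV fluids have no baseline value.

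**Causal role of between-cycle IV fluids**

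4. The Background names dehydration as a serious consequence of chemotherapy-induced nausea and vomiting (CINV). IV fluids are plausibly given because CINV was severe, which places the covariate downstream of one primary outcome.
5. The other primary outcome is any unplanned emergency or hospital admission (Health Care Resource Use). IV fluids given during such an admission could be counted in the covariate, so the model might partly adjust that outcome for itself.

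**Causal role of home antiemetics**

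6. Taking medication is among the behaviours that the game teaches. An antiemetic taken is also coded as a self-management strategy on the Symptom Management Checklist, which is a secondary outcome.
7. The medical-record list names discharge prescriptions. The covariate may therefore be a prescription count, and the article does not say when that count is fixed.

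**Illustration A: IV fluids purely a consequence of severity**

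Inputs from Power Analysis and Sample Size: true difference 1 point, SD 2.44, so the shift is 1/2.44 = 0.41 SD. Assumed: severity is normal, and the chance of IV fluids is logistic in severity, with coefficient 1.2 or 2.0 per SD (odds ratio e^1.2 = 3.3 or e^2.0 = 7.4). The overall share receiving fluids is varied. Linear regression of severity on arm and fluids, by large simulation:

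| Odds ratio per SD | Share with IV fluids | Adjusted estimate (true −1.00) |
|---|---|---|
| 3.3 | 7% | −0.93 |
| 3.3 | 28% | −0.81 |
| 3.3 | 45% | −0.78 |
| 7.4 | 10% | −0.82 |
| 7.4 | 30% | −0.67 |
| 7.4 | 44% | −0.64 |

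Across these cases the estimate shrinks by 7% to 36%.

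**Illustration B: why direction is not fixed**

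Let the arm shift the covariate by a. Let a share s of a total effect of −1 run through it. Let an unmeasured severity factor have loading c on the covariate (residual SD 1) and raise the outcome by 1 point per SD. The adjusted coefficient is then −(1 − s) − c·a.

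- a = −0.5, c = 0.5, s = 0: −1 + 0.25 = −0.75 (attenuated).
- a = −0.5, c = 0.5, s = 0.5: −0.5 + 0.25 = −0.25 (strongly attenuated).
- a = +0.5, c = 0, s = 0.5: −0.50 (attenuated).
- a = +0.5, c = 0.5, s = 0: −1 − 0.25 = −1.25 (overstated).
- a = +0.5, c = 0.5, s = 0.25: −0.75 − 0.25 = −1.00 (the two distortions cancel).

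Simulation with 250 per arm agrees (−0.76, −0.25, −0.50, −1.24 and −1.01). The values of a, c and s are assumptions; the article gives none of them.

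**The case against.** The strongest reply concerns home antiemetics. The article records antiemetics taken separately, on the checklist, and its medical-record list refers to prescriptions. Standard care includes a treatment planning visit before treatment, and staff record the treatment plan at enrolment. A clinician's prescription count set at that stage would not be changed by a game that the patient plays later, and adjusting for it would be harmless. This stands, so for this variable the defect depends on its definition. It is not settled in the trial's favour either, since discharge follows randomisation and no time is fixed.

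A second reply is that the game teaches drinking, not IV hydration. That also stands: nothing in the article makes IV fluids a direct route by which the game works. It does not rescue the covariate, because a consequence of the outcome distorts the contrast just as a mediator does.

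A third reply is that an unseen analysis plan may handle this. The article does not leave the matter open, however: it names the covariates and applies them to all models.

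A reader might infer more, namely that the trial faces a quantified loss of power and a probable false negative. The documents do not support that. They give neither the share of the effect passing through these variables nor the frequency of IV fluids. Adjustment for a consequence of severity also reduces residual variance, so a smaller coefficient need not mean much lower power. Nor does the argument reach Aim 1 in this form, since that aim is within-group and has no randomised contrast to distort.

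**Conclusion.** The point holds for between-cycle IV fluids in the Aim 2 models. That the variable arises after randomisation follows from the article's own timeline. That the arm affects it is plausible rather than demonstrated, and rests on its being a consequence of CINV severity and of unplanned care. If the arm does affect it, the coefficient is not the total effect of assignment.

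For home antiemetics the point is conditional. It holds for antiemetics taken, or for prescriptions written or changed after randomisation, and fails for a count fixed beforehand.

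Size and direction cannot be derived from the documents. Attenuation is plausible and occurs throughout Illustration A, but Illustration B shows that overstatement is possible. Both sets of numbers show only what assumed inputs would produce and do not predict this trial's result.

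**What to change.** In Data Analysis, Aim 2, replace the carry-over of the Aim 1 list with a statement that all models adjust only for variables fixed before randomisation. Specifically:

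- Delete IV fluids received between cycles.
- Keep home antiemetics only as the number prescribed before randomisation, and define it so.
- Take cancer type, emetic potential and treatment frequency as planned at T1, since later changes to the treatment plan are recorded separately.
- Analyse later IV fluids and antiemetic use as outcomes in their own right, or in an exploratory mediation analysis kept apart from the efficacy estimate.

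The cost is a sentence or two in the analysis section. The efficacy models need no new data and trial conduct does not change. The article expects data collection and analysis to be complete in 2027, so the change should be recorded before any between-arm results are seen.

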## Methods

### Study Design

Using a randomized clinical trial, we will enroll older adults from 2 clinical sites in Florida. Participants will be randomized to either the IG or attention control group (ACG). The IG will receive the MAH at baseline, and the ACG will receive it at the end of the study. Data will be collected over 6 months or 6 chemo cycles (T_2_-T_6_). Data related to CINV severity, self-management, functioning, QOL, and health care use at baseline and at the 6 time points will be collected from both groups.

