### Settings

The intervention will be offered at outpatient treatment centers at a community cancer center in Orlando, Florida, and a Comprehensive Cancer Center in Miami, Florida, that provide care to over 6000 adults aged 60 years and older each year. These numbers indicate an ample sampling pool of older adults diagnosed with cancer.

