### Data Collection

Once enrolled in the study (T_1_—baseline), research assistants will electronically record information about the participants’ diagnosis and treatment plan collected from medical records. Participants in both groups will complete baseline questionnaires electronically on an iPad given to them by the research assistant. The research assistant will demonstrate how to complete the electronic questionnaire and assist with any questions or issues that may occur during data collection. The research assistant will also meet with participants at subsequent treatment cycles (T_2_-T_6_) to have them fill out the electronic questionnaires on the iPad. Assistance will be given as needed.

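### The counted 12-covariate list for all efficacy models leaves out study site and cancer stage; adding them is nearly free and would gain a little precision if they are prognostic

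*Protocol article*

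**What the plan says.** The Aim 1 analysis text names and counts the covariates for every model. Its experiential part reads "5 experiential (cancer type, emetic potential, treatment frequency, intake of IV fluids between treatment cycles, and number of home antiemetics) variables". The demographic part covers seven variables: age, gender, race or ethnicity, comorbidity, and three socioeconomic items (education, income, insurance). The Aim 2 text, which governs the between-group comparison, carries the list over: "All models will control for the effects of demographic and experiential variables listed in aim 1". Neither site nor stage appears among the 12.

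Elsewhere the article shows that both variables exist in the trial:
- Study Design: "we will enroll older adults from 2 clinical sites in Florida". Settings describes these as "a community cancer center in Orlando, Florida, and a Comprehensive Cancer Center in Miami, Florida".
- Experiential Characteristics: "Experiential characteristics include cancer diagnosis and stage", to be taken from the electronic medical record.
- Data Collection: at baseline, "research assistants will electronically record information about the participants" covering diagnosis and treatment plan. Stage is not named in that sentence.

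Recruitment, Randomization, and Procedures describes stratification of the sampling, aimed at demographic targets, and allocation by a chosen envelope. It states no stratification of the randomisation by site or by stage. The Overview of the Data Analysis plans a descriptive check of baseline comparability.

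**The concern.** The list is enumerated and applied to all models, so this is a choice the article has made and not a detail it leaves open. Site is known at randomisation and stage is a pre-treatment characteristic, so both are legitimate baseline covariates. The list takes five experiential variables but passes over stage, which the article itself classes as experiential.

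Site could matter for both primary outcomes. The two centres differ in type. Emergency and inpatient use is self-reported and verified against records only where possible, and the centres keep their own record systems. Whether outcomes do differ by site or stage is not stated.

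At stake is efficiency. A prognostic baseline variable left out of the model stays in the error term, and a chance difference in its distribution between arms is not adjusted for. Timing also matters: adding site or stage after the baseline comparison has been seen would look data-driven, whereas adding it now would not.

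**Working it through.** **Inputs from Power Analysis and Sample Size (Aim 2).** 250 per group, difference of 1 point, SD 2.44, significance level .05, stated power 87%. The Aim 2 analysis is two-tailed.

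**Inputs that are assumptions.** The article gives no effect of site or stage. I take the extra R² from both, beyond the 12 covariates, as 1% to 10%. For imbalance I take a 50:50 site split, unrestricted allocation, and a between-site difference of 0.5 to 1.0 nausea point.

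**1. The plan's own power figure.** For one measurement per person, SE = 2.44 × √(2/250) = 0.218. Then 1/0.218 − 1.960 = 2.62, so power is 99.6%, not 87%. Averaging 6 or 30 measures with correlation 0.1 gives more than 99.9%. Random-slope variants range from 7% to 100% depending on time coding and contrast, and none tried fell within 2 points of 87%. The time coding and the software procedure are not given, so this is non-reproduction and not a demonstrated error. The point here does not rest on it; 87% is only the starting value below.

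**2. Precision for CINV severity.** At 87% power the standardised effect is 1.960 + 1.126 = 3.086. Adjustment multiplies the residual SD by √(1 − R²), so power = Φ(3.086/√(1 − R²) − 1.960). The sample giving the same precision as 500 without adjustment is 500 × (1 − R²).

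| Assumed extra R² | Power | Gain (points) | Equivalent N |
|---|---|---|---|
| 0% | 87.0% | – | 500 |
| 1% | 87.3% | 0.3 | 495 |
| 2% | 87.7% | 0.7 | 490 |
| 5% | 88.6% | 1.6 | 475 |
| 10% | 90.2% | 3.2 | 450 |

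From the 99.6% of step 1 instead, an R² of 10% gives 99.8%, so there is almost nothing to gain.

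As a guide to what R² site alone could supply: a 50:50 factor shifting severity by d explains 0.25 × d²/2.44². That is 1.0% for d = 0.5 and 4.2% for d = 1.0, before any overlap with the 12 covariates.

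**3. Chance imbalance.** The SD of the between-arm difference in site share is √(2 × 0.5 × 0.5/250) = 0.0447. A difference of 5 points or more is 0.05/0.0447 = 1.12 SD, which occurs in 26% of trials; 8.8 points or more occurs in about 5%. At 8.8 points, the unadjusted contrast moves by 0.088 × 0.5 = 0.04 to 0.088 × 1.0 = 0.09 point, against a target of 1. In units of the 0.218 standard error this is 0.2 to 0.4.

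**4. Health care use.** Two independent logistic simulations were run (4,000 trials per setting, n = 500, assumed control risk about 20%, assumed treatment odds ratio 0.5). With assumed odds ratios of 2.4 for site and 3 for stage, adding both raised power from 77.0% to 79.9% in one run and from 73.9% to 76.4% in the other. With odds ratios of 2 and 2 the rises were 77.9% to 78.6% and 76.7% to 77.5%. Type I error was about 4.5% to 4.6%. The absolute levels differ between runs, but both put the gain at about 1 to 3 points. Neither run includes the 12 planned covariates, so these gains do not measure the increment beyond them.

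**The case against.** The strongest reply is that nothing here is wrong. The plan prespecifies 12 covariates, including cancer type, emetic potential, treatment frequency and comorbidity. Race or ethnicity, insurance and income may already carry part of any difference between centres. The selection also follows the article's own rationale, since the Background names type of chemotherapy and out-of-pocket antiemetic cost as risk factors for undertreatment. Chance imbalance is already reflected in the standard error, and a shift of 0.2 to 0.4 standard errors in an unlucky trial is modest. All of this stands, and it keeps the point small.

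A reader might infer more than the article supports:
- **That site and stage likely predict both primary outcomes.** No section says so. The separate databases at the two universities share one structure, so they are no evidence of a site effect. Eligibility also narrows stage by excluding people with end-stage disease and under six months to live.
- **That envelope allocation fails to balance site.** The article does not say how envelopes were prepared. Equal numbers per centre would tend to balance it, so the 26% and 5% figures hold only for unrestricted draws.
- **That adjustment is the only remedy left for the 130 people enrolled by July 2023.** This rests on the same guess about the envelopes.
- **That stage is already held for everyone.** Collection is planned; completeness is not reported.

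Stage also has no single scale across mixed cancer types, so it needs a stated coding. None of this is a reason to leave out site, which is known for every participant.

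**Conclusion.** The point holds as an inexpensive improvement. The enumerated list omits site and a collected pre-treatment variable, stage, and it governs every between-group model. One might read the omission as biasing the treatment effect or invalidating the test. It does neither: allocation is randomised, no stratification by site or stage is stated that the model would have to reflect, and simulated type I error stays near 5%.

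The loss is conditional and small: about 0.3 to 3 power points for severity over the assumed R² range, starting from the stated 87%, and less if true power is higher. For health care use the simulated gain is of similar size, but it probably overstates the increment because the 12 covariates are absent. The case is firmer for site than for stage.

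**What to change.** In the Aim 1 covariate sentence, which Aim 2 inherits, add study site as a fixed effect and baseline cancer stage. Prespecify a coarse coding of stage that works across cancer types, for example metastatic versus non-metastatic, and say how missing stage will be handled. If either variable is left out on purpose, state why. If allocation was in fact organised by site, say so; site then belongs in the model for that reason too.

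The cost is one or two sentences, one parameter for site and one for a two-level stage variable, and possibly some missing stage values. The odds ratio for health care use becomes conditional on two more variables. The change should be fixed before any baseline comparison by arm is examined.

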##### Health-Related QOL

The European Organization for Research and Treatment of Cancer-30 [56] will measure QOL at each treatment cycle. This frequency is consistent with other studies that have measured QOL in older adults over time [57,58]. This well-known scale includes 5 functional scales, 3 symptom scales, and 6 single items using a 4-point Likert scale (1=not at all to 4=very much), and 2 global health or QOL items using a 7-point Likert scale (1=very poor to 7=excellent). Higher scores on the functional and health or QOL scale indicate better functioning, while higher scores on the symptom-related scales and items indicate higher symptoms. The tool was previously shown to be reliable in studies with older adults (Cronbach α=0.89) [56] and had a Cronbach α of 0.80 in our pilot study.

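### The named covariate list for the Aim 2 models omits the participant's own baseline functioning and QOL scores, which costs some precision, mainly at the first follow-up

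*Protocol article*

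**What the plan says.** The Study Design section of the protocol article says that data on "functioning, QOL, and health care use at baseline and at the 6 time points will be collected from both groups". Data Collection confirms this for the questionnaires: "Participants in both groups will complete baseline questionnaires electronically on an iPad given to them by the research assistant". Recruitment, Randomization, and Procedures gives the order: "baseline measures will be completed, and participants will be randomized (IG and ACG) to either group by choosing an envelope". The T1 score is therefore available in both arms and precedes allocation. The Health-Related QOL section says that the questionnaire, which contains functional as well as global QOL scales, "will measure QOL at each treatment cycle".

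Under Data Analysis, Aim 2 hypothesises higher functioning and QOL in the intervention arm at T2-T6 and fits generalized linear mixed models with a time-by-treatment term. On covariates it states "All models will control for the effects of demographic and experiential variables listed in aim 1". The Aim 1 text gives that list by count and name: "All models will control for the effects of 7 demographic (age, gender, race or ethnicity, comorbidity, education level, income level, and insurance status) and 5" variables on the treatment experience, namely type of cancer, emetogenicity, treatment frequency, IV fluids between cycles and number of antiemetics at home.

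No baseline outcome score is on the list. The Overview of the analysis plans a check of baseline comparability but attaches no adjustment to it.

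**The concern.** In a randomised trial with repeated scores, the baseline value of the outcome is a natural adjustment variable. It is measured before allocation, it is already in the database, and it removes the part of follow-up variance that it predicts. The plan puts twelve other variables in every model and does not mention this one.

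The standard errors of the T2-T6 differences may then be larger than the data require. If the arms happen to differ at T1, part of that difference also appears in the follow-up contrasts. The protocol reports small pilot effects, with QOL among the outcomes concerned, so precision that costs nothing has value. Fixing the adjustment in advance also avoids a choice made after the comparability check has been seen.

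**Working it through.** **The plan's own figure.** No Aim 2 power is stated for functioning or QOL, so there is no figure to reproduce for these outcomes. The one Aim 2 figure is 87% for nausea severity (250 per group, difference 1, SD 2.44). A plain two-sample formula gives 1/(2.44 × √(2/250)) = 4.58, and Φ(4.58 − 1.96) = 99.6%. The plan's figure comes from a mixed model whose time scale is not given, so this mismatch does not show it to be wrong. Nothing below uses it.

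**Inputs, from Power Analysis and Sample Size.**
- Aim 1, continuous outcomes: correlation of T1 with T2-T6 of 0.4, 0.16, 0.064, 0.0256 and 0.0102.
- Aim 2: within-participant correlation 0.1.
- 250 per group.
- Assumption, not in the document: a correlation that does not decay, at 0.3, 0.5 or 0.7.

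**Formulas.** These are for a linear model with equal variances over time and complete data. Each gives variance relative to the unadjusted difference in level at a visit with correlation ρ to T1.
- Adjusted for T1: 1 − ρ².
- Change from T1: 2 − 2ρ.
- T2-T6 mean, adjusted: (V − c²)/V, where V is the variance of the five-visit mean and c is its covariance with T1.
- T2-T6 mean, as change: (V + 1 − 2c)/V.

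**Mean of T2-T6, Aim 1 continuous correlations.** V = [5 + 2(4×0.4 + 3×0.16 + 2×0.064 + 0.0256)]/25 = 0.379. c = (0.4 + 0.16 + 0.064 + 0.0256 + 0.0102)/5 = 0.132. c²/V = 0.0174/0.379 = 0.046.

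**Mean of T2-T6, correlation 0.1.** V = (1 + 4×0.1)/5 = 0.28. c²/V = 0.01/0.28 = 0.036.

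| Variance relative to unadjusted | T2 | T3 | T4 | T5 | T6 | T2-T6 mean |
|---|---|---|---|---|---|---|
| Aim 1 continuous, adjusted | 0.840 | 0.974 | 0.996 | 0.999 | 1.000 | 0.954 |
| Aim 1 continuous, change | 1.20 | 1.68 | 1.87 | 1.95 | 1.98 | 2.94 |
| Aim 2 (0.1), adjusted | 0.99 | 0.99 | 0.99 | 0.99 | 0.99 | 0.964 |
| Aim 2 (0.1), change | 1.80 | 1.80 | 1.80 | 1.80 | 1.80 | 3.86 |
| Assumed constant 0.3, adjusted | 0.91 | 0.91 | 0.91 | 0.91 | 0.91 | 0.795 |
| Assumed constant 0.5, adjusted | 0.75 | 0.75 | 0.75 | 0.75 | 0.75 | 0.583 |
| Assumed constant 0.7, adjusted | 0.51 | 0.51 | 0.51 | 0.51 | 0.51 | 0.355 |

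At T2, under the Aim 1 continuous correlations, an unadjusted contrast with 500 participants is as precise as an adjusted one with 500 × 0.84 = 420.

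**Chance imbalance.** The 95% range of the baseline difference is ±1.96 × √(2/250) = ±0.175 SD. The part carried into an unadjusted follow-up difference is ρ times that:
- Aim 1 continuous correlations: 0.4 × 0.175 = 0.070 SD at T2 and 0.002 SD at T6.
- Aim 2 correlation of 0.1: 0.018 SD at each visit.
- Assumed constant 0.5 to 0.7: 0.088 to 0.123 SD at each visit.

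**If T1 is already a response.** With separate arm means at T1 and complete data, the fitted level differences at T2-T6 are still the plain follow-up differences. The time-by-treatment contrast against T1 does remove imbalance, but as a change score. Its variance, 2 − 2ρ, exceeds 1 − ρ² by (1 − ρ)², so it is less efficient at any ρ below 1.

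**The case against.** **T1 may already be in the model.** The list is not said to be exclusive, and how T1 enters a longitudinal model is a detail that an article may leave to the analysis plan. The Aim 2 sample size also counts from 6 measurements upward, while T2-T6 is five visits, which hints that T1 is a response. This stands as a hint only. Study Design speaks of baseline and six further time points, so the count settles nothing. If the hint is right, the interaction test already deals with imbalance. What remains is the lower efficiency of a change score and the unadjusted level differences that Aim 2 names.

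**The size depends on which correlation is used.** This stands. The power section gives 0.5 decaying by half per visit for a count outcome, with QOL as its example, but that is an Aim 1 calculation. The Aim 2 calculation uses 0.1. A reader might combine 0.5 with the 87% power, get a 25% variance cut at T2, and conclude that QOL power would rise to Φ(3.086/√0.75 − 1.960) = 94.6%. The documents do not support that. The 87% belongs to nausea severity, and the Aim 1 text assigns ordinal regression to QOL. The 1 − ρ² rule is a linear-model result. In an ordinal mixed model, a prognostic covariate also changes the conditional effect being estimated.

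**The outcomes are secondary, and the unadjusted comparison is valid.** Both are true, and they limit the weight of the point.

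**Conclusion.** The point holds as a modest loss of precision. Baseline functioning and QOL are collected before randomisation in both arms, and the counted, named list for all Aim 2 models leaves them out. For functioning, on the plan's own correlations, adjustment would cut variance by 1% to 16% at T2, 1% to 3% at T3 and at most 1% from T4. For the T2-T6 mean the cut is 4% to 5%. Larger gains at later visits need a correlation that does not decay, which is an assumption. No exact power gain can be stated for QOL. All figures ignore variance that the twelve listed covariates already explain.

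A reader might go further and infer that the Aim 2 estimates are biased, or that a baseline difference passes in full into every follow-up contrast. Neither is supported. Randomisation keeps the unadjusted comparison unbiased on average, and an observed imbalance carries forward only in proportion to ρ. On the plan's decaying correlations that is close to nothing by T5-T6.

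**What to change.** State in the Aim 2 paragraph how T1 enters the functioning and QOL models, in one of two forms:
- Use T2-T6 as the response, and add that scale's T1 score and its interaction with visit to the listed covariates.
- Keep T1 as a response, with the two arms' T1 means constrained equal.

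If QOL stays ordinal, say that its treatment effect is conditional on the baseline score.

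The cost is a sentence of wording before the data are analysed and a few degrees of freedom per model with 500 participants. No new data are needed. Missing T1 scores need handling in the first form, for example by simple imputation. The second form keeps those participants. A site indicator, and pre-chemotherapy nausea in the CINV severity model, are optional additions and not part of this point.
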